### Sample size

In the first stage, 20 patients will be accrued. If there are five or fewer responses, the alternative hypothesis will be rejected and the study will be stopped. If there are 13 or more responses, the null hypothesis will be rejected. Otherwise 20 additional patients will be accrued for a total of 40 patients (Table 2). Simon’s 2-stage Optimum design [18] will be used.

**Table 2 Tab2:** Simon’s 2-stage optimum design

Optimal two stage design	Optimum design
First stage sample size (n1)	20
a1	6
b1	12
Maximum sample size (n)	40
b2	17

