### Data analysis

The goal of the proposed trial is to determine the efficacy of the proposed combination sequence of anti-PD-1 treatment and radiotherapy. The primary endpoint is the objective response rate as per RECIST v1.1. The null hypothesis that the true response rate is 0.34 [3] will be tested against a one-sided alternative. The null hypothesis will be rejected if 18 or more responses are observed in 40 patients.PFS is defined from the day of randomization until progression or last follow-up. Cases will be censored at last follow up visit if no progression was observed. Multivariate analysis will be performed according to the Cox-Regression method.For the evaluation of immunological markers over time, differences between groups will be tested by using the Friedman test. To compare proportions of categorical variables, the Pearson’s Chi^2^ test or Fisher’s Exact test will be used. To evaluate correlations, Spearman correlation coefficients will be calculated. All statistical analyses will be done on an ‘intention-to-treat’ basis and performed using SPSS 24.0 (SPSS Inc, Chicago, IL, USA), a P-value less than 0.05 will be considered statistically significant.

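### The stage 1 futility limit is five responses in the text, but Table 2 prints an undefined a1 = 6 that can be read as stopping at six; separately, the design does not match the name Simon's optimum

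*Protocol article*

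**What the plan says.** The Sample size section of the protocol article sets out the rule in words.

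- Stage 1: "In the first stage, 20 patients will be accrued".
- Futility: "If there are five or fewer responses, the alternative hypothesis will be rejected and the study will be stopped".
- Efficacy: "If there are 13 or more responses, the null hypothesis will be rejected".
- Continuation: "Otherwise 20 additional patients will be accrued for a total of 40 patients (Table 2").
- Design name: "Simon’s 2-stage Optimum design [18] will be used". The Trial design section and the Discussion also call it a Simon two-stage optimal design.

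Table 2 lists n1 = 20, a1 = 6, b1 = 12, n = 40 and b2 = 17, with no key to a1, b1 or b2.

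The Data analysis section gives the null: "The null hypothesis that the true response rate is 0.34 [3] will be tested against a one-sided alternative". It gives the final rule as: "The null hypothesis will be rejected if 18 or more responses are observed in 40 patients". The article states no alternative response rate, no power and no type I error specific to the design.

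**The concern.** The text and the table it cites print different numbers against the same boundary. The only key to the table's notation is its other two limits, and these point to stopping at six or fewer, one more than the text allows.

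This limit decides whether 20 more patients are enrolled. Six of 20 is 30%, below the 34% null, and it is one of the likeliest stage 1 results if radiotherapy adds nothing. If the question were first raised with 6 of 20 in hand, the answer would be chosen with the data known.

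A second, separate matter is the design's name. A reader who sees Simon's optimum will assume a futility-only first stage and the smallest expected size under the null for the stated error rates. The printed rule has an efficacy stop as well, and the inputs needed to check optimality are not given.

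**Working it through.** **1. Text against table**

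| Boundary | Text | Table 2 | Meaning of the table value |
|---|---|---|---|
| Final | reject at 18 or more of 40 | b2 = 17 | last value that does not reject |
| Stage 1 efficacy | reject at 13 or more of 20 | b1 = 12 | last value that does not reject (also the last that continues) |
| Stage 1 futility | stop at 5 or fewer of 20 | a1 = 6 | last value that stops (conflicts with the text), or first value that continues (agrees) |

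**2. Inputs**

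From the article: n1 = 20, n = 40, efficacy stop at 13, final rejection at 18, p0 = 0.34. Assumed: an alternative rate of 0.54, because the article gives none. Let X1 be the stage 1 responses, X2 the responses among the second 20, and f the futility limit (stop if X1 ≤ f).

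**3. The outcome affected**

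From the binomial(20, 0.34) distribution:

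- P(X1 ≤ 5) = 0.276
- P(X1 = 6) = 0.178
- P(X1 ≤ 6) = 0.276 + 0.178 = 0.454
- P(X1 ≥ 13) = 0.0045

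Only seven responses (0.184) is likelier than six. At 0.54, P(X1 = 6) is 0.018.

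**4. Expected size under the null**

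E[N] = 20 + 20 × [1 − P(X1 ≤ f) − P(X1 ≥ 13)]

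- f = 5: 20 + 20 × (1 − 0.2758 − 0.0045) = 34.4
- f = 6: 20 + 20 × (1 − 0.4540 − 0.0045) = 30.8

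**5. Type I error and power**

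P(reject) = P(X1 ≥ 13) + Σ, over k from f + 1 to 12, of P(X1 = k) × P(X2 ≥ 18 − k)

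| | f = 5 (text) | f = 6 (a1 as last stopping value) |
|---|---|---|
| Stopping for futility at 0.34 | 0.276 | 0.454 |
| Expected size at 0.34 | 34.4 | 30.8 |
| Type I error at 0.34 | 0.098 | 0.095 |
| Power at 0.50 | 0.784 | 0.774 |
| Power at 0.54 | 0.902 | 0.895 |
| Power at 0.55 | 0.922 | 0.916 |

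After 6 of 20, final rejection needs 12 or more of the next 20. The chance of that is 0.015 at 0.34 and 0.38 at 0.54.

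**6. The name of the design**

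Simon's optimal design stops at stage 1 only for futility and minimises the expected size under the null for a given alpha, power and alternative rate. An exhaustive search at p0 = 0.34 assumed alternative rates from 0.50 to 0.60, alpha 0.05 and 0.10, power 0.80 and 0.90, and up to 60 patients. It returned no optimum with n1 = 20 and n = 40. Two examples:

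- Alternative 0.54, alpha 0.10, power 0.90: stop at 6 or fewer of 18, reject at 20 or more of 46, expected size 29.6.
- Alternative 0.55, alpha 0.05, power 0.80: stop at 6 or fewer of 16, reject at 18 or more of 38.

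A direct comparison with the text's rule: stopping at 7 or fewer of 21 and rejecting at 19 or more of 43 gives type I error 0.0974, power 0.9225 at 0.55 and null expected size 30.35. The text's rule gives 0.0979, 0.9221 and 34.39. A futility-only design at least as good on type I error and power, with a smaller null expected size, existed at all nine alternative rates tried from 0.42 to 0.65. With the limit at six, one existed at eight of the nine (not at 0.60).

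**The case against.** The strongest reply is that the words settle the rule. Five or fewer stops, 13 or more rejects, and everything else continues, so six continues. Table 2 has a reading that fits this exactly: a1 = 6 and b1 = 12 are the inclusive ends of the continuation range. This stands. A reader might infer that the protocol contradicts itself outright, or that the trial has no rule for six responses; the article does not go that far. What remains is a table, cited for the rule, whose undefined symbol gives a different limit under the convention its b2 row follows.

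A reader might also infer that the limit should be six, because that stops more often when the combination adds nothing. The documents do not show that six was intended, and how to trade early stopping against power is the sponsor's choice.

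Nor does the design's name create the doubt about six responses. That comes only from a1, and the two points stand apart.

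On the name, the alternative rate and power are unstated and may be in the full protocol. The source cited for the design in the Sample size section, with its notation and its criterion for optimum, is not at hand. The search therefore shows non-optimality only for the values assumed. The efficacy stop also matters little numerically: removing it changes type I error by 0.0005 (0.0979 to 0.0974) and power at 0.54 by 0.0003 (0.9018 to 0.9015). It is still not part of the design named.

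**Conclusion.** The point holds as an unreconciled boundary: five in the text, and an undefined 6 in Table 2 that, on the pattern of b1 and b2, reads as stopping at six. It is a probable notation slip or off-by-one, not a proven contradiction.

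Its effect is confined to one stage 1 result, with probability 0.18 at 0.34 and 0.02 at an assumed 0.54. The final inference is nearly the same either way: 0.003 in type I error and 0.007 in power at 0.54. What changes is early stopping under the null, by 18 percentage points, and the null expected size, by 3.6 patients. The null figures rest only on the article's own numbers; the power figures rest on the assumed alternative.

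The label Simon's optimum is inaccurate because of the efficacy stop. Failure of the sample sizes to be optimal is shown only over the alternative rates, alphas and powers searched.

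**What to change.** Before the stage 1 look:

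1. The sponsor states which futility limit was intended and approved, and the text and Table 2 are made to agree.
2. A note under Table 2 defines a1, b1 and b2, saying for each whether it is the last value on one side of the boundary or the first on the other.
3. The design is described as a two-stage design with stopping for futility and for efficacy, in place of Simon's optimum, in the Sample size section, the Trial design section and the Discussion.
4. The article or full protocol states the alternative rate, and the type I error, power and expected size that the rule delivers. With the text's rule, type I error at 0.34 is about 0.098 and null expected size is 34.4.

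The cost is wording only if the text's limit is confirmed. If the sponsor confirms six as the intended limit, power falls by about 0.7 percentage points at an assumed 0.54 (0.902 to 0.895) relative to the text's rule.

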### Data analysis

The goal of the proposed trial is to determine the efficacy of the proposed combination sequence of anti-PD-1 treatment and radiotherapy. The primary endpoint is the objective response rate as per RECIST v1.1. The null hypothesis that the true response rate is 0.34 [3] will be tested against a one-sided alternative. The null hypothesis will be rejected if 18 or more responses are observed in 40 patients.PFS is defined from the day of randomization until progression or last follow-up. Cases will be censored at last follow up visit if no progression was observed. Multivariate analysis will be performed according to the Cox-Regression method.For the evaluation of immunological markers over time, differences between groups will be tested by using the Friedman test. To compare proportions of categorical variables, the Pearson’s Chi^2^ test or Fisher’s Exact test will be used. To evaluate correlations, Spearman correlation coefficients will be calculated. All statistical analyses will be done on an ‘intention-to-treat’ basis and performed using SPSS 24.0 (SPSS Inc, Chicago, IL, USA), a P-value less than 0.05 will be considered statistically significant.

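### The 18-of-40 rejection rule has a one-sided type I error of about 0.10, but the only significance level stated is 0.05 and the primary test is not exempted from it

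*Protocol article*

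**What the plan says.** The null hypothesis is set in the Data analysis section of the protocol article: "The null hypothesis that the true response rate is 0.34", which "will be tested against a one-sided alternative". The final decision rule follows: "The null hypothesis will be rejected if 18 or more responses are observed in 40 patients". Table 2 agrees, with b2 = 17.

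The Sample size section gives the stage 1 rules. "In the first stage, 20 patients will be accrued". "If there are five or fewer responses, the alternative hypothesis will be rejected", and the trial stops. "If there are 13 or more responses, the null hypothesis will be rejected" (Table 2: b1 = 12). Otherwise 20 more patients are enrolled, 40 in all. Table 2 lists a1 = 6, whereas the text stops at five or fewer.

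The last sentence of the Data analysis paragraph opens with "All statistical analyses will be done on an" intention-to-treat basis, names the software, and closes with "a P-value less than 0.05 will be considered statistically significant". No other significance level appears in the article.

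**The concern.** A decision rule stated as a count implies a type I error, and here the count and the stated significance level do not match. If the 0.05 threshold applies to the primary test, a final count of 18 (45%) rejects the null by one sentence of the paragraph and is not statistically significant by another. If it does not apply, nothing in the article says so, and a reader would take a rejection as a 5% result when the false-positive risk is about twice that. This is the trial's only primary test, and the Discussion presents the design as a step before larger randomised trials, so the strength of evidence behind a positive result should be clear.

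**Working it through.** **Inputs.** p0 = 0.34, one-sided, final rejection at 18 or more of 40 (Data analysis; b2 = 17 in Table 2). Stage 1: n1 = 20, early rejection at 13 or more (Sample size; b1 = 12). Futility stop at five or fewer (Sample size text) or six or fewer (one reading of a1 = 6 in Table 2); both are computed. The article states no type I error for the rule, so there is no design figure to reproduce first.

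**Formula.** With X1 and X2 independent Binomial(20, p) and a the futility limit,

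P(reject) = P(X1 ≥ 13) + Σ over x1 = a+1 to 12 of P(X1 = x1) × P(X2 ≥ 18 − x1).

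**Type I error at p = 0.34.** P(X1 ≥ 13) = 0.0045. The remaining terms are:

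| x1 | P(X1 = x1) | P(X2 ≥ 18 − x1) | product |
|---|---|---|---|
| 6 | 0.1782 | 0.0154 | 0.0027 |
| 7 | 0.1836 | 0.0434 | 0.0080 |
| 8 | 0.1537 | 0.1032 | 0.0159 |
| 9 | 0.1056 | 0.2087 | 0.0220 |
| 10 | 0.0598 | 0.3624 | 0.0217 |
| 11 | 0.0280 | 0.5460 | 0.0153 |
| 12 | 0.0108 | 0.7242 | 0.0078 |

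- Futility at five or fewer: products sum to 0.0934; 0.0934 + 0.0045 = **0.0979**.
- Futility at six or fewer (drop the x1 = 6 row): 0.0979 − 0.0027 = **0.0952**.
- Check ignoring the stages: P(X ≥ 18 | n = 40, p = 0.34) = 0.0981.

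The disagreement between text and table on futility therefore barely matters here.

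**One-sided P at each final count.** The two-stage P ranks early rejection as more extreme than any final count, so it equals the type I error of a rule with that cut-off. The normal approximation uses mean 40 × 0.34 = 13.6 and SD √(40 × 0.34 × 0.66) = 2.996. For 18 responses, uncorrected, z = (18 − 13.6)/2.996 = 1.469. With continuity correction, z = (17.5 − 13.6)/2.996 = 1.302.

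| Responses | Two-stage exact (futility ≤5 / ≤6) | Exact, ignoring stages | Normal, corrected | Normal, uncorrected |
|---|---|---|---|---|
| 18 | 0.098 / 0.095 | 0.098 | 0.097 | 0.071 |
| 19 | 0.054 / 0.053 | 0.053 | 0.051 | 0.036 |
| 20 | 0.028 / 0.028 | 0.027 | 0.024 | 0.016 |

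At 18 every method gives P above 0.05. At 19 the exact methods are just above it and the uncorrected approximation is below. At 20 all agree with the rule.

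**How often the trial would finish there** (futility at five or fewer). The chance of exactly 18 is the rejection probability with cut-off 18 minus that with cut-off 19; for 18 or 19, subtract that with cut-off 20. The article gives no target rate, so the rates other than 0.34 are assumptions.

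| True rate | cut-off 18 | cut-off 19 | cut-off 20 | exactly 18 | 18 or 19 |
|---|---|---|---|---|---|
| 0.34 | 0.0979 | 0.0543 | 0.0284 | 4.4% | 7.0% |
| 0.45 | 0.5593 | 0.4364 | 0.3210 | 12.3% | 23.8% |
| 0.50 | 0.7835 | 0.6829 | 0.5675 | 10.1% | 21.6% |
| 0.54 | 0.9018 | 0.8376 | 0.7511 | 6.4% | 15.1% |

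At rates above the null, the three cut-off columns are also the power of each rule.

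**The case against.** The strongest defence is that the primary endpoint has its own rule, a count, given identically in the Sample size table and the Data analysis text. The article never says that a P-value will be calculated for it. The 0.05 clause comes last, after the Cox, Friedman, chi-squared, Fisher and Spearman methods, and shares its sentence with the software version, so it can be read as a general threshold for those analyses. A specific boundary would ordinarily prevail over a general sentence. The boundary also looks like a coherent design: type I error just under 0.10 and power about 0.90 at a rate near 0.54. One-sided 0.10 can be a legitimate choice in phase II.

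Most of this stands. A reader might infer that the boundary was miscalculated. The documents do not support that, because the article never claims that 18 of 40 is a 5% rule. Nor is it a finding that power and a target rate are absent, since a condensed article may leave those to the full protocol. A reader might also infer that 18 and 19 responses both lead to opposite conclusions. That is secure only at 18; at 19 it turns on which test is used, and the article names none for the primary endpoint.

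What the defence does not remove is that the closing sentence speaks of all analyses, contains the only significance level in the document, and does not except the primary test. The intended 0.10 is itself an inference from the numbers.

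**Conclusion.** The point holds as a conflict between a stated decision threshold and a stated significance level. The 18-of-40 rule carries an exact one-sided type I error of 0.098, or 0.095 with futility at six or fewer, against 0.05. The conflict is definite at 18 responses and marginal at 19. The chance of finishing at exactly 18 is about 4% under the null and 6% to 12% at assumed true rates of 0.45 to 0.54.

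The figures rest on p0 = 0.34, 20 + 20 patients, early rejection at 13 or more, and all 40 patients being evaluated when the trial continues. Neither reading of the futility limit changes the conclusion. It does not follow that the boundary is wrong or that the trial needs more patients. The defect is one of wording and should be corrected, but it does not invalidate the design.

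**What to change.** Keep the boundary at 18 of 40. State in Data analysis that the primary two-stage test is one-sided with alpha of about 0.10 (exact 0.098, or 0.095 if futility is at six or fewer). Limit the 0.05 sentence to the secondary and exploratory analyses. Do this before stage 1 results are known, since a choice made after seeing 18 or 19 responses would be driven by the data. The futility limit in the Sample size text and a1 in Table 2 should be reconciled at the same time, so that one exact alpha can be quoted.

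The cost is a few words and no patients; the downside is a less favourable stated false-positive rate.

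If the sponsor did intend 5% for the primary test, the smallest exact boundary is 20 of 40, because 19 gives 0.053 to 0.054. That rule has an exact alpha of 0.028. Its power falls from 0.78 to 0.57 at an assumed rate of 0.50, and from 0.90 to 0.75 at 0.54. This is a trade-off for the sponsor to weigh and is not the recommended change.

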### Trial design

This phase II trial assesses the response rates of the anti-PD-1/SBRT combination. Nivolumab or pembrolizumab will be administrated according to the recommended dosing schedule. Prior to the 2nd cycle, SBRT will be delivered (24 Gy in three fractions) to the largest (max. diameter of 5 cm) fluorodeoxyglucose (FDG)-avid metastatic lesion. Table 1 shows a general scheme of the trial.

**Table 1 Tab1:** General scheme of the trial

	Run-in period	Study period	Observation period	
SBRT		Three fractions of 8 Gy every other day		
Anti-PD-1 treatment	First cycle		Second cycle	Continuation

This trial uses a Simon two-stage optimal design, a design often used for phase II cancer clinical trials [12]. This design allows the assessment of the efficacy of a combination therapy in a relatively small number of patients.

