#### Secondary endpoints

Objective response rate of the non-irradiated metastases as determined by immune related response criteria (irRC) [14].Metabolic response of the irradiated and non-irradiated metastases based on the European Organization of Research and Treatment of Cancer (EORTC) 1999 criteria [15].Local control defined as the time between local irradiation and the moment the irradiated lesion shows an increase in size of ≥20%, according to the RECIST V1.1, confirmed by a consecutive assessment at least 4 weeks after first documentation.PFS: two types of PFS will be defined. One as the time from inclusion to documented disease progression according to RECIST v1.1 or death from any cause. The other as the time from inclusion to documented disease progression according to irRC or death from any cause.Acute and late toxicity due to the combination treatment will be scored using the Common terminology criteria for adverse events (CTCAE) version 4.0.

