### Evaluation and randomization

Patients must be restaged within 4 weeks prior to randomization with an 18F-FDG Positron emission tomography with X-ray computed tomography (PET/CT).

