## Discussion

Although current immunotherapeutic treatment options have led to an important breakthrough in patients with metastatic melanoma, they still fail to induce long-lasting clinical benefit in the majority of patients. We hypothesize that combining anti-PD-1 treatment with radiotherapy might result in improved clinical response rates and PFS compared to anti-PD-1 treatment in monotherapy. Both preclinical and retrospective clinical data support this hypothesis. The current study is an innovative translational phase II design translating preclinical data to the clinic. By using a Simon two-stage optimal design, the study will allow the assessment of the efficacy of a combination therapy in a relatively small number of patients before embarking on more expensive randomized trials. In addition, the translational focus on immunologic markers might be suitable for identifying mechanisms of response and resistance to therapy, resulting in predictors for efficacy and improved patient selection for future clinical applications.

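### The Data analysis section drops death as a PFS event and dates PFS from a randomization the trial does not describe, contradicting the protocol's own endpoint definition

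*Protocol article*

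**What the plan says.** The Secondary endpoints section of the protocol article defines two versions of PFS. The first is "One as the time from inclusion to documented disease progression according to RECIST v1.1 or death from any cause"; the second is "The other as the time from inclusion to documented disease progression according to irRC or death from any cause". Both start at inclusion and both count any death.

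The Data analysis section gives one version only: "PFS is defined from the day of randomization until progression or last follow-up". It adds: "Cases will be censored at last follow up visit if no progression was observed". Death is not named as an event, and the censoring rule makes no exception for it.

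Randomization also serves as a date in the section Evaluation and randomization: "Patients must be restaged within 4 weeks prior to randomization". No arms, allocation ratio or allocation procedure appear anywhere. The Trial design section states: "This trial uses a Simon two-stage optimal design, a design often used for phase II cancer clinical trials". Efficacy is judged against a fixed rate: "The null hypothesis that the true response rate is 0.34 [3] will be tested against a one-sided alternative". The Discussion places randomization after this study, which is meant to assess efficacy "before embarking on more expensive randomized trials".

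**The concern.** Two sections of the same document give different rules for the same endpoint. An analyst who programs from the Data analysis section would estimate time to progression with deaths censored and report it as PFS. Patients who die before progression is documented have among the worst outcomes, and these are the events that would be lost.

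The protocol's follow-up makes such deaths plausible. After the week 6 PET/CT, the Follow-up section leaves imaging to the treating physician and ends it at progression or when treatment stops. A patient who stops treatment for toxicity or another illness can therefore die with no progression on record.

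The Discussion hypothesizes better PFS than with anti-PD-1 monotherapy. With no concurrent control, that comparison can only be made with outside data. If those data count deaths as events, a curve that censors them would flatter the combination.

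Separately, a start date that the design does not produce leaves time zero undefined on the literal text.

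**Working it through.** The document states no PFS median, rate or event count, so there is no figure to reproduce. The check is a comparison of the texts, followed by the direction and possible size of the effect.

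**1. The two definitions side by side**

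| Element | Secondary endpoints | Data analysis |
|---|---|---|
| Time zero | Inclusion | Day of randomization |
| Events | Progression or any death | Progression |
| Death without documented progression | Event | Censored at last visit |
| Versions | RECIST v1.1 and irRC | One, criteria not named |

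**2. Direction.** Take one death without progression and change it from an event to a censored time at the date of death. The Kaplan-Meier curve then loses one downward step. It is unchanged before that date and higher afterwards, unless both curves are already at zero.

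One refinement applies because the written rule censors at the last visit, which comes before the death. Suppose n patients are at risk at that visit, k others then progress, and the patient then dies, with no other censoring in between. Relative to its level at the visit, the curve is:

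- between the k-th progression and the death: (n−k)/n if the death will count, (n−1−k)/(n−1) if the patient has been censored;
- after the death: (n−k−1)/n against (n−1−k)/(n−1).

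With n = 40 (the maximum sample size) and k = 3 (assumed), this gives 37/40 = 0.925 against 36/39 = 0.923 before the death, and 36/40 = 0.900 against 36/39 = 0.923 after it. Early removal can lower the curve very slightly between the last visit and the death. From the death onward the curve is too high.

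**3. Size, on assumed inputs only.** Let h be the constant total hazard of a PFS event and s the share of PFS events that are deaths without progression. Censoring those deaths at the date of death leaves hazard (1−s)h, so

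median = ln 2 / [(1−s)h] = true median × 1/(1−s).

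| s (assumed) | 1/(1−s) | Inflation | Reported median if the true median is 6 months (assumed) |
|---|---|---|---|
| 5% | 1/0.95 = 1.053 | +5% | 6.3 months |
| 15% | 1/0.85 = 1.176 | +18% | 7.1 months |
| 25% | 1/0.75 = 1.333 | +33% | 8.0 months |

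The percentage inflation does not depend on the assumed median. At s = 0 it is zero.

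**4. Finite-sample check.** Trials of 40 patients were simulated with exponential PFS, a true median of 6 months, administrative censoring between 12 and 36 months, and deaths censored at their own date. There were 2000 trials for each of four values of s, 8000 in all. Mean estimated PFS at month 6, with deaths counted and then with deaths censored, was 0.497 and 0.514 (s = 5%), 0.502 and 0.538 (10%), 0.501 and 0.575 (20%), and 0.501 and 0.616 (30%). The formula 0.5^(1−s) gives 0.518, 0.536, 0.574 and 0.616. In none of the 8000 trials was the month 6 estimate lower with deaths censored.

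**5. The start date.** Inclusion criteria require radiological studies within 28 days before registration. Evaluation and randomization sets a 4-week restaging window before randomization. 4 × 7 = 28 days, so the windows are the same length, which suggests that randomization stands for registration. If so, the wording has little or no numerical effect.

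**The case against.** The strongest reply is that the dedicated endpoint section already states PFS correctly, twice, and that the Data analysis sentence is a loose restatement. PFS is one of several secondary objectives, with no hypothesis, threshold or power attached. Stopping and rejection depend only on response counts. All of this stands and limits the severity. It does not remove the conflict: these are two stated rules that disagree, not a detail left to another document.

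Several stronger readings are tempting and are not supported.

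- *The start date also biases PFS upward.* A reader might infer this because both faults sit in one sentence. Nothing in the documents gives the start date a direction, and it is most likely a slip.
- *Censoring at the last visit instead of the last scan is a further contradiction.* No section sets another censoring date for living patients. The last tumour assessment is a common convention, but with discretionary imaging after week 6 it could fall well before the last visit. It is a choice, not a correction.
- *The Cox results are biased in favour of the combination.* The Cox model would use the same event indicator, but there is no treatment contrast, and covariate hazard ratios could move either way or not at all.
- *The error always favours the combination.* If no patient dies without documented progression, there is no effect.

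**Conclusion.** The contradiction is real and lies in the current text. Following Data analysis literally turns deaths without documented progression into censored times, so PFS is overstated from the date of any such death. The illustrated inflation of the median, +5% to +33% for s from 5% to 25%, rests on constant hazards, censoring at the date of death and values of s that the documents do not give. It shows what is possible, not what to expect.

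The use of randomization as a date is a wording fault. The protocol never calls itself single-arm; that is inferred from the two-stage design, the fixed reference rate, the absence of any allocation and the Discussion.

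This should be fixed. A reader might infer that it threatens the trial's main conclusion, but PFS is secondary and the primary response-rate rule does not use it.

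**What to change.** In Data analysis, replace the two PFS sentences with the endpoint definition, for example: PFS runs from the date of inclusion to the first documented progression or death of any cause, whichever comes first, analysed once with progression by RECIST v1.1 and once by irRC; only patients alive without progression are censored.

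State the censoring date for those patients. The last visit may be kept. The last tumour assessment is an option, but it changes the rule and would need a definition of an adequate assessment.

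Replace randomization with inclusion or registration, using one term throughout, in Data analysis and in Evaluation and randomization, including that heading.

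Aligning the event definition and the term needs no extra patients, visits or scans. Reported PFS will be shorter than under the present rule if any patient dies without documented progression, by an amount that depends on how many do. The change should be made before PFS is analysed, so that the definition is not chosen with results in view.
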